***Randomization***

To minimize selection bias and accidental bias, Patients were randomly allocated to endoscopic evacuation group, aspiration group, or small boneflap craniotomy group in 1:1:1 ratio using a central randomization system based on computer-generated number sequence after a written informed consent was signed. Neither the neurosurgeons nor the patients could know the grouping beforehand. Randomization must take place within 24 hours of ictus and patients will be operated on within 12 hours of randomization. During the randomization process the neurosurgeon is informed of the treatment group the patient is allocated to and should record this. Best medical treatment must begin as soon as possible and continue throughout follow-up in all patients.

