**Surgical procedures**

***Endoscopic evacuation***

In this intervention group, patients will receive endoscopic surgery under general anesthesia. A 4-5cm skin incision is made according to the position of hematoma on brain CT scan. The approaches include the middle frontal gyrus approach for anterior basal ganglia hemorrhages that are not elongated but rather are more spherical. A parietooccipital small boneflap is created to treat posterior basal ganglia and thalamic hemorrhages. In cases involving superficial lobar hemorrhages, use a small boneflap directly at the location where the lesion comes closest to the surface. Then make a bone flap about 2cm in diameter and incise the dura mater in a cruciate fashion. Use a new-developed endoscopic introducer (China National Invention Patent: 201210066281.1) to make an appropriate working channel for the endoscope. First, impale the blunt puncturing lever in a predetermined position and then pull out the inner core. Second, suck with a syringe to determine whether the puncture lever has been in the right place. After confirmation, place the transparent cannula along the puncture lever. Through the space made by the transparent introducer, we can carefully evacuate intracerebral hematoma under the surveillance of endoscope. Plasminogen activator (urokinase) will not be injected after endoscopic surgery.

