***Stereotactic aspiration***

In the aspiration group, the target point was set at near the posterior edge of the hematoma chosen on CT scan image with the largest expansion of hematoma. First, the patient undergoes a brain CT scan with slice thickness <5mm and the CT image data in Digital Imaging and Communications in Medicine (DICOM) format will be collected. Available commercial neuro-navigation or free mobile-device-based navigation was recommended in all centers to improve accuracy of catheter puncture. The target point is chosen on the CT scan with the largest expansion of the hematoma and special attention was paid to stay away from important cortex function areas. Hematoma aspiration was done with a 10 mL syringe until first resistance. After confirmation of catheter by postoperative CT, urokinase of 30,000 units every 12h was injected through the catheter to dissolve residue hematoma for 3-5 days. Catheter was removed when there was no more blood drained or the catheter had been placed for up to 5 days.

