**Outcomes measurements**

The primary outcome of this study is the degree of disability estimated using the modified Rankin Scale (mRS) 6 months after ictus. An unfavorable outcome is defined as death or dependency with a mRS of 3-6. Living patients’ independence in activities of daily lives and quality of life will be a highlight of this study. We will also measure patients’ quality of life and their performance in activities of daily living using the Barthel Index at 6-months follow-up. Secondary outcomes also include: hematoma clearance rate evaluated at 72h after surgery, operation time, intraoperative blood loss, postoperative GCS score 7 days after surgery, rebleeding rate, days of NICU stay, intracranial infection rate during hospitalization, 1 month mortality, 3 months mortality, hospitalization expenses, and Barthel Index at 6 months.

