**Statistical analysis**

Statistical analysis will be on a “intention to treat” basis. Measurement data will be described using mean and standard deviation or median and interquartile range while count data will be described using indexes such as percentage, ratio and relative risk. The primary analysis will be a simple categorical frequency comparison using the Chi-squared test for prognosis based favorable and unfavorable outcomes at 6 months. The continuous variables will be analyzed by One-way ANOVA. Logistic regression analysis will be undertaken for age, gender, hematoma volume, preoperative GCS, surgical method, and intracranial infection. All statistical analyses will be performed using SPSS statistics 26.0 (IBM Corp. USA). A value of two side P <.05 was considered statistically significant.

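### The only multivariable model places intracranial infection, a post-randomisation secondary outcome, beside surgical method, so its surgical-method odds ratio is not the total effect of allocation

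*Protocol*

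**What the plan says.** The Statistical analysis section names one multivariable analysis: "Logistic regression analysis will be undertaken for age, gender, hematoma volume, preoperative GCS, surgical method, and intracranial infection". It gives neither the dependent variable nor the purpose of the model. The same section makes an unadjusted test primary: "The primary analysis will be a simple categorical frequency comparison using the Chi-squared test".

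The Outcomes measurements section counts "intracranial infection rate during hospitalization" among the secondary outcomes. The Randomization section fixes the order of events: "Randomization must take place within 24 hours of ictus and patients will be operated on within 12 hours of randomization".

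The Surgical procedures section describes arms that differ in ways that could affect infection. For aspiration, urokinase is instilled through a catheter every 12 hours, and "Catheter was removed when there was no more blood drained or the catheter had been placed for up to 5 days". For endoscopy, "Plasminogen activator (urokinase) will not be injected after endoscopic surgery". For craniotomy, a catheter is placed only if needed.

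**The concern.** A covariate used to adjust a randomised comparison should be fixed before allocation. Age, gender, hematoma volume and preoperative GCS meet that condition. Infection does not: it follows surgery, may depend on the technique, and may itself lead to death or dependency. Holding it constant has two consequences.

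- Any harm or benefit of a technique that acts through infection is taken out of that technique's odds ratio.
- Unmeasured features that make a patient prone both to infection and to a poor outcome become associated with arm once infection is held fixed. The balance given by randomisation is then lost within infection strata.

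This is the protocol's only adjusted estimate for surgical method. If it differs from the chi-squared result, readers are likely to take it as the refined answer, although it answers a different question.

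**Working it through.** The protocol states no figure for this point, so there is none to reproduce. The check has a timing step and an illustration of size.

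**Step 1. Timing and role of each term in the model (from the protocol)**

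| Term | When fixed | Role |
|---|---|---|
| Age, gender, hematoma volume, preoperative GCS | before surgery | baseline covariates |
| Surgical method | at randomisation | randomised factor |
| Intracranial infection | in hospital, after randomisation | secondary outcome |

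Infection is the only term that allocation can influence.

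**Step 2. Planning odds ratio without infection**

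The Sample size section assumes 33% unfavourable with craniotomy and 21% with minimally invasive surgery.

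OR = (0.21/0.79) / (0.33/0.67) = 0.2658 / 0.4925 = 0.540, so log OR = −0.617.

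**Step 3. Odds ratio with infection in the model**

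The arm totals stay at 33% and 21%. Let i be the infection rate in an arm and R the odds ratio of infection for an unfavourable outcome. Both are assumptions, since the protocol gives neither. For each arm, solve for p, the risk in uninfected patients:

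(1 − i)·p + i·p* = arm total, where p*/(1 − p*) = R·p/(1 − p).

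The surgical-method odds ratio from the model is then the ratio of the uninfected odds in the two arms. Baseline covariates and shared causes are left out of this illustration.

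Worked case: infection 10% with craniotomy, 3% with minimally invasive surgery, R = 4.
- Craniotomy: p = 0.2969, p* = 0.6281; 0.90 × 0.2969 + 0.10 × 0.6281 = 0.330.
- Minimally invasive: p = 0.2010, p* = 0.5015; 0.97 × 0.2010 + 0.03 × 0.5015 = 0.210.
- OR = (0.2010/0.7990) / (0.2969/0.7031) = 0.596.
- Share of the log OR removed: 1 − ln(0.596)/ln(0.540) = 16%.

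All cases (the value without infection is 0.540 throughout):

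| Infection, craniotomy vs minimally invasive | R = 2 | R = 4 | R = 8 |
|---|---|---|---|
| 10% vs 3% | 0.568 | 0.596 | 0.620 |
| 10% vs 5% | 0.558 | 0.574 | 0.584 |
| 5% vs 2% | 0.551 | 0.561 | 0.568 |
| 5% vs 5% | 0.538 | 0.531 | 0.521 |
| 2% vs 5% | 0.526 | 0.507 | 0.487 |
| 5% vs 10% | 0.516 | 0.485 | 0.448 |
| 3% vs 10% | 0.509 | 0.470 | 0.429 |

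**Step 4. Reading the table**

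- More infection after craniotomy: the model understates the benefit. At 10% vs 3%, 8% to 22% of the log OR is removed.
- More infection after minimally invasive surgery: the model drops a harm and overstates the benefit. At 5% vs 10%, the log OR grows by 7% to 30%.
- Equal rates: the change is small (0.521 to 0.538). It is not mediation. Odds ratios shift when any prognostic variable is added, even one balanced across arms, and some of the movement in the other rows has the same source.

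**The case against.** Four points on the other side deserve an answer.

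**The main conclusion is safe.** This stands. The chi-squared comparison keeps everything that acts through infection, and infection and mortality are reported separately. A reader might infer that the trial's primary result is biased, or that harm from infection vanishes from the report. The protocol does not support that; one supporting coefficient is affected.

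**The model may be meant to find prognostic factors.** Surgical method is fifth of six listed variables, and no outcome or purpose is named. This stands in part. A multivariable model for the 6-month outcome is still the natural reading, and nothing tells readers not to take the surgical-method coefficient as a treatment effect. A statistical analysis plan might settle the purpose, but the protocol already fixes the covariate list.

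**The shift may be small.** With 240 per arm, the standard error of the log OR is √[1/(240 × 0.33 × 0.67) + 1/(240 × 0.21 × 0.79)] = √(0.0188 + 0.0251) = 0.21. Most shifts in the table are below that: ln(0.620/0.540) = 0.138 and ln(0.448/0.540) = −0.187. Only the most extreme case exceeds it, at ln(0.429/0.540) = −0.230. The magnitude is fairly called uncertain. However, the shift is systematic and does not shrink as patients are added.

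**Intention to treat is kept.** A reader might infer that the model breaks the stated intention-to-treat basis. That is not shown. Every patient can still be analysed in the allocated arm; what changes is the meaning of the coefficient, not the analysis set.

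**Conclusion.** The point holds for the logistic model and goes no further. As listed, the covariates make the surgical-method odds ratio a quantity conditional on a post-randomisation outcome, so it does not estimate the total effect of allocation. That follows from the covariate list and the order of events, on the reading that the model is for the 6-month unfavourable outcome.

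The size does not follow from the protocol. Under the assumed infection rates (2% to 10% per arm) and infection odds ratios (2 to 8), the planning value of 0.54 moves to roughly 0.45 to 0.62, and to 0.43 at 3% vs 10% with an infection odds ratio of 8. The direction depends on which arm has more infection, so the model cannot be called conservative. It is tempting to say flatly that the model removes part of the treatment effect, but that requires infection to differ between arms and to affect outcome. The protocol makes a difference plausible and gives no data on either.

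**What to change.** In the Statistical analysis section:

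- Name the dependent variable (unfavourable outcome at 6 months) and state that the model gives a covariate-adjusted estimate of the surgical-method effect.
- Delete intracranial infection from that model. Keep surgical method and the baseline covariates already listed: age, gender, hematoma volume and preoperative GCS.
- Analyse infection by arm as the secondary outcome it already is.
- If a model containing infection is wanted, label it an exploratory prognostic-factor model and state that no treatment effect will be drawn from it.

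The cost is a phrase or two of text. No extra patients, data or visits are needed, and the primary analysis does not change.

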**Data monitoring and quality control**

The data monitoring committee considers data from interim analyses and reports to the Trial Steering Committee. Interim analyses are strictly confidential and the committee will only recommend stopping the trial early if one or other treatment show an advantage at a very high significance level. The coordinating center (Chinese PLA General Hospital, Beijing) is responsible for maintaining computerized databases containing all data related to the trial, the quality of computerized information, conducting statistical analyses, preparing reports for the data monitoring committee, and all correspondence in relation to the trial. To better control the quality of this study, all neurosurgeons performing the operation have got a short-term centralism training before the trial begins.

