**Study design**

This is a multicenter, randomized, controlled, open-label, sequentially designed non-profit study (ClinicalTrials.gov ID: NCT02811614) involving 16 neurosurgical centers. Patients with newly diagnosed supratentorial HICH according with our inclusion criteria will be enrolled in this study. A follow-up period of 6 months will be sufficient enough to show outcome and prognosis of surgical treatment. A flowchart of this study is shown in Figure 1.

[figure not shown]

Figure 1 Flow chart of the study design

The trial will be conducted in the departments of neurosurgery at 16 Chinese hospitals: (1) Chinese PLA General Hospital, Beijing; (2) Jingzhou Central Hospital, Hubei province; (3) Wuhan No.1 Hospital, Hubei province; (4) Jinzhou Central Hospital, Liaoning province; (5) Yichang Central People’s Hospital, Hubei province; (6) Hainan Hospital of Chinese PLA General Hospital, Hainan province; (7) Liaoning Thrombus Hospital, Liaoning province; (8) Jiangmen Central Hospital, Guangdong province; (9) People’s Hospital of Sanshui District. Foshan, Guangdong province; (10) Minzu Hospital of Guangxi Medical University, Guangxi province; (11) The Second Hospital of Jilin University, Jilin province; (12) Jilin Province People’s Hospital, Jilin province; (13) Siping Central People’s Hospital, Jilin province; (14) Tangdu Hospital of Air Force Military Medical University, Shanxi province; (15) The Third Affiliated Hospital of Inner Mongolia Medical University, Inner Mongolia; (16) The First Affiliated Hospital of Xinjiang Medical University, Xinjiang province. All neurosurgeons taking part in the MISICH study have been trained by an annually held national continuing education program by Chinese PLA General Hospital about endoscopic evacuation, stereotactic aspiration, and small boneflap craniotomy. These three surgical techniques have been routinely used in all centers prior to the start of trial.

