**Sample size and randomization**

***Sample size***

It was reported that the rate of unfavorable outcome of patients receiving craniotomy with a supratentorial hematoma volume >30 ml was 49% to 67% and minimally invasive surgeries might decrease the rate of unfavorable outcome by about 8% to 22% compared with craniotomy. Our recent retrospective study showed that endoscopic surgery lowered the risk of unfavorable outcome in patients with supratentorial HICH by nearly 28% in comparison with craniotomy. We assume that the endoscopic surgery and stereotactic aspiration could reduce the risk of unfavorable outcome from 33% to 21%. A sample size of 720 (240 in each group) would be required to show a 12% benefit from minimally invasive surgery with 90% power and a type I error probability of .05 with a 10% dropout rate taken into consideration.

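### The early-stopping rule holds harm to the same very strict evidence as benefit, gives no route for harm common to all arms, and is worded for two treatments in a three-arm trial

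*Protocol*

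**What the plan says.** Early stopping is covered only in the protocol's Data monitoring and quality control section. It describes the committee's remit as "The data monitoring committee considers data from interim analyses and reports to the Trial Steering Committee" and then states that "the committee will only recommend stopping the trial early if one or other treatment show an advantage at a very high significance level". It gives no number for the level, no number or timing of looks, and no separate criterion for safety.

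Two other sections bear on how the rule reads. Study design calls the trial a "randomized, controlled, open-label, sequentially designed non-profit study", so interim looks are part of the design. Randomization allocates patients to "endoscopic evacuation group, aspiration group, or small boneflap craniotomy group in 1:1:1 ratio", so there are three active surgical arms and three possible pairwise comparisons.

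Outcomes measurements lists rebleeding, intracranial infection, and mortality at one and three months. None of these is linked to the stopping rule.

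**The concern.** A very strict interim level is a sensible guard against stopping too soon on a claim of superiority. The evidence needed to protect patients from a worse procedure need not be as strong. By saying that the committee will recommend stopping *only* on such an advantage, the protocol applies one bar to both purposes. This is a stated restriction, not a detail left open: a charter or SAP with a milder safety criterion for stopping the trial would contradict the protocol.

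Three consequences follow:

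- Excess deaths, rebleeding or infection in one arm must reach the benefit level before they support a recommendation to stop.
- Harm common to all three arms gives no arm an advantage, so the literal rule never applies to it.
- The phrase about one or other treatment presupposes two treatments. With three arms it does not say which comparison triggers the rule. Stopping the whole trial is the only recommendation named, and closing one arm while the others continue is not addressed.

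At stake is continued randomisation to a surgical arm with a marked but not extreme excess of deaths, unless someone acts outside the stated rule.

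**Working it through.** The protocol gives no boundary to reproduce, so the check shows how large a harm must be to meet the rule under stated assumptions.

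**Inputs**

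- From Sample size: 240 patients per arm, 10% dropout, and 33% unfavorable outcome under craniotomy.
- Assumed: one look at the halfway point, so 0.5 × 240 × 0.9 = 108 evaluable per arm; one pairwise comparison.
- Assumed: *very high* means two-sided p < .01, < .005 or < .001.
- Assumed for illustration: one-month deaths of 28/108 against 13/108 (26% against 12%). These rates are not in the protocol.

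**1. The example against the rule**

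- Pooled rate = 41/216 = .190.
- SE = √(.190 × .810 × 2/108) = .0534.
- Difference = 15/108 = .139.
- z = .139/.0534 = 2.60, two-sided p = .009.

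This meets the rule at .01 and fails it at .005 and .001.

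**2. Excess needed to cross** (critical value × SE, pooled rate held at 19%)

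| Level | Critical value | 108 per arm | 120 per arm |
|---|---|---|---|
| .01 | 2.576 | 13.7 points | 13.0 points |
| .005 | 2.807 | 15.0 points | 14.2 points |
| .001 | 3.291 | 17.6 points | 16.7 points |

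The last column drops the 10% loss, which may be too heavy for one-month mortality; its SE is .0506. In whole deaths, with 13 in the comparator and the pooled rate recalculated, 32 deaths at 108 per arm still fail at .001 (p = .0015). The first count to cross is 33 (p = .0009), an excess of 20/108 = 18.5 points.

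**3. Chance of crossing when the harm is real**

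Probability = 1 − Φ[(c × SE₀ − δ)/SE₁], where c is the critical value, δ the true difference, SE₀ the pooled SE and SE₁ = √[(p₁q₁ + p₂q₂)/n].

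For true one-month mortality of 26% against 12%, δ = .14, SE₀ = .0534 and SE₁ = .0525:

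- At .01: (2.576 × .0534 − .14)/.0525 = −0.05, giving about 52%.
- At .001: (3.291 × .0534 − .14)/.0525 = 0.68, giving about 25%.

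The same formula on the primary outcome, with 33% unfavorable in the comparator and 108 per arm:

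- An arm 12 points worse crosses 22% of the time at .01 and 7% at .001.
- An arm 20 points worse crosses 66% and 37% of the time.

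**4. What a strict interim level does to type I error**

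This was simulated with equally spaced looks, interim p < .001, final p < .05 and two to four looks in total. One pairwise comparison keeps an error of about 5.0% to 5.1%. Two techniques each compared with a shared craniotomy arm give about 9.1% to 9.2% for at least one false positive. The strict level therefore costs almost nothing per comparison, but it does not control error across both.

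**The case against.** A reader might infer that a serious harm signal in one arm cannot trigger any action. The protocol does not support that, for three reasons.

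- All three arms are active surgeries and the rule is symmetric. Excess death in one arm is an advantage for its comparator, so a large enough excess does meet the rule.
- The restriction covers recommendations to stop the trial. The committee also reports to the Trial Steering Committee, and nothing bars it from raising a safety concern there.
- Closing one arm while two continue is arguably not stopping the trial. It is unaddressed, not forbidden.

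It can also be said that boundaries, safety triggers and the number of looks commonly sit in an SAP or charter, which is not at hand. That is fair, and the absence of those details is not part of this point. The exclusive wording and the two-treatment phrasing are in the protocol itself, however, and another document could not relax them without contradiction.

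Finally, the size depends on what *very high* means. The 28 against 13 example passes at .01 and fails at .001, so no single figure should be quoted as the protocol's own. This stands, and it is why a range is given.

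**Conclusion.** The point holds in a limited form. Under the protocol's wording, harm supports a recommendation to stop the trial only at the benefit threshold, harm common to all arms has no route, and the rule does not say which of three comparisons it governs.

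The size is illustrative. It rests on an assumed halfway look, one pairwise comparison, about 19% pooled one-month mortality and an assumed level between .01 and .001. On that basis, an excess of roughly 14 to 18 percentage points in one-month mortality would be needed, and a true 14-point excess would be missed at that look about half the time at .01 and three times in four at .001.

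A reader might also conclude that, with a strict interim level, a final test at .05 is sound for the whole design. That holds for each comparison taken alone. The overall error of about 9% for two comparisons with craniotomy is a separate multiplicity question, which this point does not settle.

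**What to change.** Reword the stopping sentence in Data monitoring and quality control in three respects:

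- Apply the very high significance level to stopping for benefit only.
- Replace the two-treatment phrase with the named pairwise comparisons that the level governs.
- State that the committee may recommend pausing or stopping the trial, or a single arm, on safety data already collected (mortality, rebleeding, intracranial infection) without meeting that level.

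Any SAP or committee charter should be brought into line. The revised text should not claim that a final .05 controls error across both comparisons with craniotomy.

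The cost is two or three sentences and a matching charter line, with no new data. The small downside is that closing an arm would leave at least one comparison incomplete.
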